#### Security index

Incidence of organ and vascular injury events related to the system, including the following: (1) whether there is an intraoperative injury of adjacent organs caused by the failure of the system, including the injury of the masseter muscle, mouth, parotid gland, etc.; (2) whether there was massive bleeding caused by vascular injury caused by functional failure of the tested system during the operation. The incidence of injury events was defined as the proportion of subjects in the experimental control group who had an injury event to all subjects.Incidence of adverse events during the trial.

An adverse event that occurs during the clinical trial, whether or not it is device-related, includes the following: (1) all suspected adverse device effects; (2) significant unrelated diseases, that is, certain symptoms or diseases that are not present at the time of entry into the study; (3) the worsening of an existing disease, that is, the simultaneous emergence of some new symptoms or signs. A pre-existing condition is defined as a condition or symptom that exists before the study begins and is initially recorded on the history/physical examination record prior to treatment; (4) accidental injury or accident; (5) any improper and unexpected event related to a medical device is an adverse device effect, that is, it is associated with the use of the study product. Any adverse event due to improper instructions for the use of a device, and any adverse event due to the user’s inappropriate operation, are included in this definition.Incidence of device failure: (1) The console and machine communication suffers substantial interference. The movement of the manipulator fails and cannot be eliminated after reset and restart; (2) surgical clamps could not release the tissue; and (3) instrument installation alarm; intraoperative failure or damage of instruments.Abnormal vital signs (body temperature, heart rate, respiration, mean arterial pressure (MAP)).

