### Interventions

#### Explanation for the choice of comparators {6b}

The patients of the control group received the mandibular distraction osteogenesis (MDO) surgery traditionally, in which the surgeon performs the osteotomy on their own experience based on preoperative design without navigation equipment. That is the most widely used method in the current operating theater.

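### The adverse-event definition counts every suspected device effect but qualifies unrelated events with an undefined 'significant', so adverse-event incidence may not be comparable between the arms

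*Protocol article*

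**What the plan says.** All of this is in the protocol article, Outcomes {12}, Security index, unless another section is named.

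- The lead-in sets relatedness aside: "An adverse event that occurs during the clinical trial, whether or not it is device-related, includes the following".
- Item (1) is "all suspected adverse device effects", with no severity limit.
- Item (2) is "significant unrelated diseases, that is, certain symptoms or diseases that are not present at the time of entry into the study". This is the only item with a word of degree, and no threshold is given for it.
- Item (3) is "the worsening of an existing disease, that is, the simultaneous emergence of some new symptoms or signs".
- Item (4) is "accidental injury or accident".
- Item (5) states that "any improper and unexpected event related to a medical device is an adverse device effect", and explains this as meaning that "it is associated with the use of the study product".

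The control arm has no such product: under Explanation for the choice of comparators {6b}, "the surgeon performs the osteotomy on their own experience based on preoperative design without navigation equipment". Who will be blinded {17a} says the operator cannot be blinded. Adverse event reporting and harms {22} has the team's clinical doctor document medical issues arising in either group, with no filter for severity or relatedness. Secondary outcomes also lists six postoperative complications, to be recorded without any condition on arm or device.

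**The concern.** The lead-in says relatedness is irrelevant to whether an event counts, but the list gives related and unrelated events different entry conditions. A suspected device effect enters however slight it is. An unrelated event meets the word 'significant', which someone must interpret.

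The split is written by relatedness, but one side of it is empty in control, because those children never have the system. The unqualified route is therefore open only in the navigation arm. A slight new symptom after a navigated cut can enter as a suspected device effect. The same symptom after a freehand cut has to be judged significant or fit another item. 'Suspected' and 'significant' are both judgements, and the staff making them may know the allocation.

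At stake is the safety comparison. Adverse-event incidence is a stated safety index and, unlike the fixed list of complications, it is open-ended. If ascertainment differs between arms, part of any difference could come from the definition, and the bias would run against navigation.

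Two other phrases are loose. Item (3) explains worsening through new symptoms or signs, which could be taken to leave out a baseline condition that only becomes more severe. Item (5) describes an adverse device effect as unexpected, which could be taken to leave out a foreseeable harm of the splint or template.

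**Working it through.** The documents state no adverse-event figure, so there is none to reproduce. The check is a reading of the text followed by an illustration on assumed rates.

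**Step 1. Routes into the count, by arm**

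| Item | Qualifier | Navigation | Control |
|---|---|---|---|
| (1) suspected device effects | none on severity | open | not available |
| (2) unrelated diseases | 'significant', undefined | open | open |
| (3) worsening of existing disease | none on severity | open | open |
| (4) accidents | none on severity | open | open |
| (5) device-associated events | 'unexpected' | open | not available |

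Items (2) to (4) apply to both arms in the same words. The only asymmetry is a new minor event that is not an accident or a worsening: it has an unqualified route in navigation and a qualified one in control.

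**Step 2. Two readings of item (2)**

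- Broad: its explanatory clause governs, so any symptom or disease absent at entry counts.
- Narrow: 'significant' governs, so minor unrelated events are left out.

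**Step 3. Illustration**

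From the protocol: 11 children per arm (Sample size {14}). Assumed, because the documents give no rates: in both arms alike, s = 10% of children have a significant event and a further share m have only a minor new one. A share q of those minor events is suspected to be device-related in the navigation arm.

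- Broad reading: s + m in both arms, so the difference is 0.
- Narrow reading: navigation s + mq, control s, so the difference is mq.

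The last column is the probability that a two-sided Fisher exact test gives P < 0.05, by exact enumeration over two independent binomials with n = 11 each.

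| m | q | Navigation | Control | Difference | Fisher P < 0.05 |
|---|---|---|---|---|---|
| any | 0 | 10% | 10% | 0 | 0.2% |
| 10% | 0.25 | 12.5% | 10% | 2.5 points | 0.3% |
| 10% | 0.5 | 15% | 10% | 5 points | 0.6% |
| 30% | 0.5 | 25% | 10% | 15 points | 3.9% |
| 30% | 1 | 40% | 10% | 30 points | 19.1% |
| 50% | 1 | 60% | 10% | 50 points | 55.9% |

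In the row with m = 30% and q = 0.5, the expected numbers of children counted are 11 × 0.25 = 2.75 against 11 × 0.10 = 1.1, although the true rates are identical.

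**Step 4. Reading the table**

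At this sample size the main effect is a biased incidence estimate. A false significant result becomes likely only when minor events are common and nearly all are blamed on the device.

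**The case against.** The strongest reply is that the protocol gives one definition for the whole trial. No item names an arm, and unrelated events in navigated children meet the same 'significant' wording. The list is introduced by 'includes', which leaves it open, and item (2) explains itself as symptoms or diseases not present at entry. On that explanation a new symptom in a control child counts and there is no distortion. Items (3) and (4) carry no severity limit; a surgical mucosal tear could enter under (4) in either arm. Lip numbness could be recorded as nerve injury among the listed complications. Section {22} has any medical issue in either group documented. Item (1) may already take in foreseeable device harms, and a condition that becomes more severe is a worsening in ordinary language.

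Most of this stands. A reader might infer that the protocol sets a different bar for each arm and that adverse-event incidence therefore cannot be compared. The text does not support that: the split is by relatedness, and it bites only on the narrow reading.

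A reader might also take a much larger false-positive risk from an extreme case. Suppose minor events occur in 40% of children in both arms, all are suspected in navigation and none counts in control. Fisher's test then gives P < 0.05 in 47% of trials, against 1.6% under a common definition. With half suspected (20% against 0%), it is 5.0%. The 47% rests on assumptions chosen at the limit. In addition, Statistical methods {20a} names its tests for primary and secondary outcomes, so a Fisher test of this index is not expressly planned.

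The reply does not remove the ambiguity. The explanatory clause speaks of 'certain' symptoms, which is itself selective, and 'significant' remains in the text. Section {22} governs documentation and reporting to the ethics committee; it does not say what counts toward the incidence, and it is wider than the definition. Severity grading may be left to the full protocol, but an entry condition stated here is not a missing detail.

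**Conclusion.** The point holds as a minor one. The definition claims indifference to relatedness and then qualifies only unrelated events, with an undefined word. Device effects can arise only in the navigation arm and the judging staff may know the allocation, so the wording permits differential ascertainment. Adverse-event incidence may therefore not be comparable between arms.

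The size cannot be derived from the documents. It is zero on the broad reading or if no minor event is attributed to the system. On the narrow reading it is mq: 2.5 to 50 percentage points over the assumed range of m from 10% to 50% and q from 0.25 to 1. The direction is against navigation. The conclusion assumes that some minor events occur, that some are attributed to the system, and that 'significant' is applied as a filter.

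The wording of items (3) and (5) does not clearly exclude pure worsening or foreseeable device harms, but it should not be left open to that use.

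**What to change.** In the Security index section, delete 'significant' from item (2) and use one definition for both arms: any new or worsened untoward medical event, regardless of severity, expectedness or relation to the system. This matches the documentation rule in section {22} and makes the list agree with its own lead-in. It also settles items (3) and (5), because an increase in severity counts as worsening and a foreseeable device harm counts as an event.

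Record severity and relation to the system as two separate fields. Report adverse device effects, expected or not, as a subset for the navigation arm. Compare the arms on all-cause incidence per child.

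The cost is one reworded paragraph and, if they are not already there, two fields on the adverse event form. The small downside is that more minor events will be recorded.

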**Fig. 3 Fig3:**
[figure not shown]
Robotic navigation-assisted MDO. **a** Surgical environment. **b** Verification of the system registration. The verification pinpointing at the registration point on the splint represents accurate registration. **c** Template in position. The surgeon is conducting osteotomy with the saw blade relying on the template. **d** Assisted osteotomy from the intraoral viewpoint. (A) Navigation system. (B) Computer base. (C) Dental splint. (D) Verification pin. (E) Electromagnetic receptor. (F) Electromagnetic generator. (G) Bone saw. (H) Template arriving at the designed osteotomy line

Before the osteotomy, the splint is mounted on the patient’s teeth as the registration piece is connected to the magnetic field of the navigation system. The 3D printed template will be clamped on the end of the robotic arm to locate precisely the osteotomy line according to the preoperative design documents stored and managed by the EM system. Then, the surgeon performs the osteotomy by moving the saw along the template (Fig. 3c, d).

The management of all patients is identical, and to reduce surgical bias, the chief surgeon in the control and experimental groups will be the same senior craniomaxillofacial specialist with more than 15 years of specialty practice and an average annual craniofacial surgery volume of 300 or more. There will be two attending surgeons assisting with the operation. The team training of the navigation-assisted surgery group is more than 100 h.

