#### Criteria for discontinuing or modifying allocated interventions {11b}

The criteria for discontinuing or modifying include the malfunction of the EM system, surgical accident, and any situation that makes the surgeon need to finish the surgery as soon as possible. The patients’ demographic data that meet those criteria will still be collected.

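### The device-failure list does not fit the navigation system under test, so whether a navigation failure is counted depends on how the list is read

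*Protocol article*

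**What the plan says.** Outcomes {12}, Security index, makes the incidence of device failure a named safety measure, and Table 1 schedules it for the day of operation. Failure is defined by a numbered list:

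- Item (1) has two parts, of which the first is "The console and machine communication suffers substantial interference".
- The second part of item (1), and then item (2), read "The movement of the manipulator fails and cannot be eliminated after reset and restart; (2) surgical clamps could not release the tissue".
- Item (3) is "instrument installation alarm; intraoperative failure or damage of instruments".

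Intervention description {11a} and the Fig. 3 legend describe the device. A splint carrying steel spheres is fixed to the teeth and registered to the magnetic field. A pin check confirms this: "The verification pinpointing at the registration point on the splint represents accurate registration". Then "The 3D printed template will be clamped on the end of the robotic arm to locate precisely the osteotomy line", and the surgeon runs the saw along that template.

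Section {11b} adds that "The criteria for discontinuing or modifying include the malfunction of the EM system, surgical accident", together with any situation that calls for a quick finish. For patients who meet these criteria, it names only demographic data as still being collected.

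**The concern.** The list and the device description do not match. The list has an item for a part that the article does not describe, and it does not name several steps on which the described system depends. A manipulator fault that stops the arm during surgery but clears on restart falls outside its own item, while an installation alarm counts without qualification. EM malfunction is serious enough in {11b} to end or change the allocated intervention, yet the failure index does not name it.

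The system is moving from animal experiments to children, and its failure rate is one of the things that this exploratory trial can usefully report. If recorders differ on what the list covers, the reported incidence depends on the recorder as well as on the device. On a narrow reading it would be too low.

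**Working it through.** **Number exposed.** Sample size {14} uses 1.99 and 1.32 mm, two-sided α = 0.05 and power 0.90. Taking 1.99 as δ and 1.32 as σ with equal allocation:

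n = [(1.960 + 1.282) / (1.99/1.32)]² × (1/0.5 + 1/0.5) × ½ = 9.25

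This reproduces the stated 9.24. Then 9.24/0.9 = 10.27, rounded up to 11 per group. So 11 children are planned to be navigated. The point does not depend on this formula beyond that count.

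**Events set against the list.**

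| Event in the described system | Listed item that might catch it | Reading |
|---|---|---|
| Pin verification fails or must be repeated | None by name; item (3) only at a stretch | Not named |
| EM tracking lost or distorted | Interference part of item (1) | Can reasonably be counted |
| Template cannot be brought to or held at the line | Item (3), if the template or arm is an instrument | Depends on reader |
| Arm stops, then clears on restart | Outside item (1); item (3) if read broadly | Depends on reader |
| Navigation abandoned for EM malfunction | None by name; items (1) or (3) if the cause fits | Depends on reader |
| Clamp does not release tissue | Item (2) | No matching part described |

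Two features of the text make the broad reading uncertain. First, the Security index elsewhere calls the tested device a system and uses the word instrument only in item (3). Second, if item (3) covered arm faults cleared by restart, the restart condition in item (1) would have no effect. The punctuation of item (1) also leaves it unclear whether that condition applies to communication interference.

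**What one event does.** Exact (Clopper-Pearson) 95% intervals with n = 11:

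- 0/11: 0%, upper limit 1 − 0.025^(1/11) = 28.5%
- 1/11: 9.1% (0.2 to 41.3%)
- 3/11: 27.3% (6.0 to 61.0%)

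**What partial capture does.** The documents give no expected failure rate, so the true rate p and the share c of failures that the list captures are assumptions. The chance of reporting none is (1 − p·c)^11:

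| p | c = 1 | c = 0.5 |
|---|---|---|
| 10% | 0.90^11 = 31% | 0.95^11 = 57% |
| 20% | 0.80^11 = 9% | 0.90^11 = 31% |
| 30% | 0.70^11 = 2% | 0.85^11 = 17% |

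**The case against.** Much can be said for the existing list, and some of it stands.

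- **Breadth of the items.** Substantial interference is wider than loss of communication and can cover lost tracking. Intraoperative instrument failure has no severity threshold and no restart condition, so it can cover some arm and template failures. This stands. A reader might infer that the trial would report no device failures while navigation was failing; the text permits that outcome on a narrow reading but does not compel it.
- **Other safety measures.** Unexpected device-related events are also adverse device effects, and injuries caused by system failure are counted separately. This stands in part. Those are different indices, and the injury index needs organ injury or massive bleeding, so neither corrects the device-failure incidence.
- **Off-plan cuts remain visible.** A reader might infer that failures putting the saw off the line would be hidden. The documents do not support this: deviation from plan is the primary outcome, measured on CT within 7 days by blinded staff, with intention-to-treat analysis. That outcome does not, however, show whether a system failure caused the deviation.
- **The restart condition is a severity threshold.** That is a legitimate choice, and a pin check that prompts re-registration before cutting may be the safeguard working. This argues for reporting such events separately, not for leaving them unrecorded.
- **No contradiction.** Section {11b} governs the intervention and the Security index governs recording, so the two can coexist. This is correct; what is missing is the link.
- **The clamp item is harmless.** A redundant item does not lower the count, and Fig. 3 is not available here. This stands as to bias, but the item still does not correspond to the device as described.
- **The intervals do not measure the defect.** They apply to any binary outcome in 11 patients. This is true; they show only how much one classification decision matters.

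**Conclusion.** The point holds as a mismatch of definition. The Security index states an explicit list, so this is not detail that a journal article has left out. As written, the list does not name failed registration or verification, template positioning failure, or navigation abandoned because of system malfunction. It counts manipulator faults only if they persist after restart, includes a clamp item with no counterpart in the described device, and is not tied to {11b}. The result can be an undercount, but whether it occurs depends on how the interference and instrument items are read.

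In size, one reclassified child moves the estimate by 9.1 percentage points (1/11). Under assumed true rates of 10% to 30%, capturing half of the failures raises the chance of reporting none from 31%, 9% and 2% to 57%, 31% and 17%. The rates and the 50% capture share are illustrative. The primary outcome is not affected. The change should be made because device failure is a named safety index with few exposed children and the correction is cheap.

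**What to change.** Redefine the index for this device and report each item as x/11 navigated patients:

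- (a) registration verification failed, with repeats that then succeeded reported separately;
- (b) splint displaced, or EM tracking lost or distorted;
- (c) template could not be brought to, or held at, the planned line;
- (d) manipulator or communication fault, split by whether restart cleared it;
- (e) navigation abandoned because of system malfunction. Abandonment for the other reasons in {11b}, such as a surgical accident or the need to finish quickly, should be recorded separately and not counted as device failure.

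Remove the clamp item, or state which part of the system it refers to. Reconcile the Security index with {11b}, so that an EM malfunction leading to discontinuation or modification is recorded under both. This changes what is recorded, not how patients are managed.

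The cost is revised protocol wording and a few extra fields on the operation-day form. The reported failure rate may look less favourable.

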### Participant timeline {13}

See the participant timeline in Table 1.

**Table 1 Tab1:** The participant and data collection timeline

**Time point**	Baseline and allocation (− day 7–0)	Operation day (day 1)	Postoperation		
			7 days	1 month	6 months
**Enrollment**					
Basic information	√				
Medical history	√				
Eligibility screen	√				
**Interventions**					
Traditional surgery		√			
Surgical robot		√			
**Primary outcome**					
Accuracy of osteotomy			√		
**Secondary outcome**					
The symmetry of mandibular					√
The pain scale evaluation			√	√	√
The postoperative complications			√	√	√
Satisfaction score			√	√	√
**Perioperative index**					
Surgical time		√			
System installation time		√			
Hospital stay			√		
Blood loss volume		√			
Drainage volume			√		
Drainage duration			√		
**Security index**					
Incidence of organ and vascular injury events related to the system		√			
Incidence of adverse events during the trial		√			
Incidence of device failure		√			
Abnormal vital signs		√			

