#### Secondary outcomes

The secondary outcome includes the symmetry of the mandibular, pain scale, recording of surgical complications, and satisfactory score.

The symmetry of the mandibular is evaluated by three indicators: the angle of inclination, the mandibular ramus’s height, and the mandibular body’s length, which will be obtained from the CT 6 months after the surgery (Fig. 4b).

The angle of inclination: A horizontal plane (HP) is established by selecting bilateral suborbital points (Or) and the healthy superior external auditory canal points (Po). Establish the occlusal plane (OP) from the adjacent medial point of the maxillary central incisor to the medial buccal cusp of the bilateral first molar. Measure the angle between the occlusal plane and the horizontal plane, set as angle A. The smaller angle A indicates the smaller deviation angle of the mandible and maxilla, meaning the better symmetry of the lower face.

The height of mandibular ramus: The height of mandibular rami, that is, the distance between condylion (Co) and mandibular gonion (Go), is measured respectively. The distance of the affected side is set as *h*, and the distance of the healthy side is set as *H*. Comparing the values of the affected and the healthy sides. The smaller the difference, the better the bilateral symmetry.

The length of the mandibular body: The menton (me) is marked, and the length of the bilateral mandibular body, the distance from the bilateral gonion (Go) to the menton (Me), is measured respectively. The distance of the affected side is set as *l*, and the distance of the healthy side is set as *L*. Comparing the values of the affected and the healthy sides, the smaller the difference, the better the bilateral symmetry.

The pain scale: The evaluation time is 1 week, 1 month, and 6 months after surgery. The pain scale is an international visual analog scale, with a scale from 0 to 10 representing no pain to the most intense pain.

The postoperative complications during the trial will be recorded, including local infection, bone nonunion, scar hyperplasia, occlusal disorder, nerve injury, and tooth germ injury.

The satisfaction score was evaluated by a modified 5-point Likert table, with 1–5 indicating unsatisfactory to very satisfied. It will be recorded at the 1-week, 1-month, and 6-month follow-up.

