### Plans to promote participant retention and complete follow-up {18b}

Children with hemifacial microsomia and their guardians are concerned about their prognosis since it affects function and appearance. Furthermore, collecting the patients’ contact information, such as their mobile phone number, WeChat ID, and email address, is common practice. Patients are also given our center’s phone number, which they may use to call our medical practitioner if they have any issues. We maintain constant contact with the patients in this manner to ensure proper follow-up. Also, certain patients must return to our facility for additional treatment of compounded issues, such as the occlusal condition. The medical team will give comprehensive pre- and postoperative care to encourage trial participants’ retention. All patients will be followed for 6 months for postoperative recovery and complications, and the PI will review the procedure and respond to the investigator’s report. The Clinical Research Center/Office of Quality Management of Shanghai 9th People’s Hospital, School of Medicine, Shanghai Jiao Tong University, will audit and verify the program’s data every quarter.

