### Adverse event reporting and harms {22}

The available literature on robotic navigation has documented no adverse outcomes in other surgical procedures. Suppose there are any medical issues in either group throughout the follow-up period. In that case, the team’s clinical doctor will document and treat them before reporting to the ethics committee a week later.

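### Table 1 schedules the trial-wide adverse event incidence on the operation day only, contradicting its own label and the text, so adverse events other than surgical complications have no scheduled assessment after day 1

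*Protocol article*

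**What the plan says.** The Security index section of the protocol article lists the incidence of adverse events as a safety measure. Its definition opens with "An adverse event that occurs during the clinical trial, whether or not it is device-related". It then names suspected device effects, diseases that were absent at entry, worsening of a condition already present, and accidents.

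The section on adverse event reporting {22} looks beyond the day of surgery. It begins "Suppose there are any medical issues in either group throughout the follow-up period" and goes on to say that such problems are documented, treated and reported to the ethics committee. The retention section {18b} sets the length of follow-up: "All patients will be followed for 6 months for postoperative recovery and complications".

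Table 1 (Participant timeline {13}) has five time columns: baseline and allocation, operation day, 7 days, 1 month and 6 months. The row "Incidence of adverse events during the trial" has one tick, in the column whose heading begins "Operation day (day 1". The later cells are empty.

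A separate secondary outcome row, "The postoperative complications", is ticked at 7 days, 1 month and 6 months. The Secondary outcomes section describes it as follows: "The postoperative complications during the trial will be recorded, including local infection, bone nonunion, scar hyperplasia, occlusal disorder, nerve injury, and tooth germ injury".

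**The concern.** The row label and the schedule cannot both be right. An incidence over the trial needs enquiry about events until the end of follow-up, yet the schedule asks for it once, on the day of surgery. Most of the categories in the definition, such as a new illness or the worsening of an existing one, are not events that one expects to find on that day.

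At stake is the meaning of a declared safety measure for a new navigation system used in children. If the case report form is built from Table 1, the figure reported under that label will rest on the operation day. Whatever else is known about later events will then come from a different outcome, or from reports made when someone happened to notice a problem. Two staff members reading the same protocol, one from the table and one from the text, would collect different data.

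**Working it through.** The plan gives no figure for this point to reproduce. The check is a reading of Table 1 column by column, set against the text.

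**Step 1. Is the tick really under the operation day?** Other rows of the table show how its positions read.

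| Row in Table 1 | Operation day | 7 days | 1 month | 6 months |
|---|---|---|---|---|
| "System installation time" (likewise surgical time, blood loss) | tick | – | – | – |
| Hospital stay, drainage volume and duration | – | tick | – | – |
| "The postoperative complications" | – | tick | tick | tick |
| "Incidence of adverse events during the trial" | tick | – | – | – |

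The adverse event row has the same layout as items that can only arise in the operating theatre. It differs from rows ticked at 7 days and from the row ticked at every postoperative visit. The position is therefore not an artefact of how the text was extracted, and the table does distinguish one-time items from repeated ones.

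**Step 2. Count the coverage.**
- Adverse event row, time points on or after surgery: 1 of 4.
- Adverse event row, postoperative visits: 0 of 3.
- Complications row, postoperative visits: 3 of 3.

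**Step 3. Which later events have a scheduled assessment?**

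| Kind of event after the operation day | Scheduled visit in Table 1 | Other provision |
|---|---|---|
| Surgical complication | 7 days, 1 month, 6 months | Sections {18a}, {19} and {22} |
| Device effect not counted as a surgical complication | none | Section {22}, if it comes to attention |
| New or intercurrent disease | none | Section {22}, if it comes to attention |
| Worsening of existing disease | none | Section {22}, if it comes to attention |
| Accident | none | Section {22}, if it comes to attention |

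Sections {18a} and {19} have surgeons record security information during follow-up. The items that they name include complication rates, but not adverse events in the wider sense.

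**Step 4. Do the other safety rows have the same conflict?** The system-related organ and vascular injury row is also ticked on the operation day only. The Security index section defines those injuries as occurring during the operation, so tick and definition agree. The device failure row is likewise largely a matter of the operation itself. The conflict is specific to the adverse event row.

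**Step 5. Scale.** The sample size section plans 11 patients per group. Assume that the incidence is the proportion of patients with at least one event; the article defines the incidence of injury events in this way but does not say so for adverse events. One patient counted or not counted then moves an arm's figure by 1/11 = 0.091, about 9 percentage points. This shows how sensitive the measure is. It does not estimate how many events would be missed.

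**The case against.** The strongest reply is that the text leaves no doubt about the intention. The row's own label, the adverse event definition, the six-month follow-up and section {22} all point to collection over the whole trial. One table cell is then most likely a tabulation slip, which staff would read past. The article is also condensed and refers readers elsewhere for the full protocol, so the visit forms in use cannot be seen. All of this is fair. It limits what can be said about the consequence, but it does not remove the contradiction: the article states a schedule, and the schedule conflicts with its own text. Section {22} does not settle it, because it sets no enquiry at a visit and does not say that what it gathers enters the Security index incidence.

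Several stronger readings are tempting, and the document does not support them.
- A reader might infer that nothing after day 1 is captured. Surgical complications are scheduled at three later visits, and section {22} covers problems that arise.
- A reader might take the six named complications as a closed list. The sentence introduces them as inclusions, so others may be recorded.
- A reader might divide one day by six months and call the result the fraction of safety observed. A tick marks a time point, not an observation window. Event risk is not uniform over follow-up either, since the system is used only during surgery.
- A reader might conclude that both arms will look safer than they are. The document gives no event rates, and whether events are lost depends on which instruction staff follow.
- A reader might want the organ and vascular injury row ticked at 7 days as well. Those injuries are defined as intraoperative, so the present tick fits.

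**Conclusion.** The point holds as an internal contradiction with a practical consequence. Table 1 places adverse event incidence at 1 of the 4 time points on or after surgery and at none of the 3 postoperative visits, while the label and the text cover the whole trial. Part of the later safety information is secured through the complications outcome and section {22}. The broader adverse event set is not scheduled after the operation day, and an incidence built on the schedule would not be an incidence over the trial.

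The reading of the tick is certain. The consequence rests on the assumption that data are collected as Table 1 says. The number of events that would go uncounted, and any difference between the arms, cannot be derived from the document. The point should be corrected, because it decides which data are collected for a declared safety measure. It does not touch the primary outcome.

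**What to change.** Reconcile Table 1 with the Security index section and section {22}:
- Tick the adverse event row at the operation day, 7 days, 1 month and 6 months, for both arms.
- State in the Security index section that the incidence is cumulative to 6 months and reported per arm.
- Leave the organ and vascular injury row as it is.

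The cost is a table correction, one sentence, and one form page at visits that already take place. Under section {25} the revision goes to the ethics committee before it is implemented.
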